## Abstract

**Background:**

Pain conditions of the musculoskeletal system are very common and have tremendous socioeconomic impact. Despite its high prevalence, musculoskeletal pain remains poorly understood and predominantly non-specifically and insufficiently treated.

The group of chronic musculoskeletal pain patients is supposed to be heterogeneous, due to a multitude of mechanisms involved in chronic pain. Psychological variables, psychophysiological processes, and neuroendocrine alterations are expected to be involved. Thus far, studies on musculoskeletal pain have predominantly focused on the general aspects of pain processing, thus neglecting the heterogeneity of patients with musculoskeletal pain. Consequently, there is a need for studies that comprise a multitude of mechanisms that are potentially involved in the chronicity and spread of pain. This need might foster research and facilitate a better pathophysiological understanding of the condition, thereby promoting the development of specific mechanism-based treatments for chronic pain. Therefore, the objectives of this study are as follows: 1) identify and describe subgroups of patients with musculoskeletal pain with regard to clinical manifestations (including mental co-morbidity) and 2) investigate whether distinct sensory profiles or 3) distinct plasma levels of pain-related parameters due to different underlying mechanisms can be distinguished in various subgroups of pain patients.

**Methods/Design:**

We will examine a population-based chronic pain sample (n = 100), a clinical tertiary care sample (n = 100) and pain-free patients with depression or post-traumatic stress disorder and pain-free healthy controls (each n = 30, respectively). The samples will be pain localisation matched by sex and age to the population-based sample. Patients will undergo physical examination and thorough assessments of mental co-morbidity (including psychological trauma), perceptual and central sensitisation (quantitative sensory testing), descending inhibition (conditioned pain modulation, the diffuse noxious inhibitory control-like effect), as well as measurement of the plasma levels of nerve growth factor and endocannabinoids.

**Discussion:**

The identification of the underlying pathophysiologic mechanisms in different subgroups of chronic musculoskeletal pain patients will contribute to a mechanism-based subgroup classification. This will foster the development of mechanism-based treatments and holds promise to treat patients more sufficient.

## Background

Chronic pain conditions of the musculoskeletal system are common and of high socioeconomic relevance [1-4]. This is especially true for pain conditions with widely unknown pathogeneses, such as non-specific chronic back pain (CBP), chronic widespread pain (CWP), and fibromyalgia syndrome (FMS). In addition, the prevalence of these conditions and the demand for consultation and treatment have increased over recent years [5,6], which results in high direct and indirect costs [1,3,7,8].

However, therapeutic approaches in chronic musculoskeletal pain patients are often of minor success [9-16]. This is likely because the aetiology and pathogenesis of chronic musculoskeletal pain are still widely unknown. As a result, treatment for this condition involves predominantly unspecific interventions, although the group of chronic musculoskeletal pain patients is believed to be heterogeneous [17,18]. Differences in response to the same treatment in patients with the same disease could be explained by different underlying mechanisms contributing to the generation and maintenance of pain [19,20]. The situation is complicated by the finding that the same disease can derive from various pathophysiological mechanisms. Conversely, the same pathophysiological mechanism may be of interest in distinct diseases [20].

The heterogeneity is supported by strong hints that subgroups exist that differ in terms of aetiopathology, clinical symptomatology, and psychophysiological patterns. A recent study revealed distinct somatosensory profiles in CBP and FMS: FMS patients showed increased sensitivity for different pain modalities in all measured body areas, which suggests central disinhibition (or a deficient pain inhibitory system) as a potential mechanism. CBP subjects, in contrast, exhibited localised alterations within the affected segment. Such alterations may be due to peripheral sensitisation [21]. This finding is in accordance with the main hypothesis of a mechanism-based diagnosis in chronic pain syndromes, which proposes that defined symptoms and signs reflect possible underlying neurobiological pain mechanisms [19,22]. Consequently, these subgroups should be treated with specific mechanism-based approaches, but to date, they have been treated with the same non-specific multimodal treatment programs. Therefore, the assessment of chronic pain and research identifying various factors associated with the development, maintenance, and spread of chronic pain, including their neurobiological correlates, is highly relevant.

Chronic pain has been found to be associated with a higher prevalence of mental co-morbidity. Patients with CBP [23,24], CWP [25], and FMS [26] suffer from mental disorders significantly more often than pain-free controls. This finding is especially true for anxiety disorders and mood disorders, which were found to have prevalence rates of 20.9% and 12.7%, respectively, in a population-based sample of patients with chronic back pain [23]. Of further interest is the role of psychological trauma, which has been neglected in previous research. Traumatic events have higher prevalence rates in patients with pain compared to pain-free controls or patients with other diseases [27-29]. Concerning traumatic experiences, it was suggested that multiple traumas have a cumulative effect on physical health, including back pain and that the impact of the trauma on health may be independent of post-traumatic stress disorder (PTSD) symptomatology [30,31].

The assessment of chronic pain and mental comorbidity on a psychobiological basis may detect common underlying pathophysiological changes. With regard to pain processing there are studies that suggest a role for central disinhibition mechanisms in depression and, to a lower extent, in patients with FMS compared to healthy controls [32]. Alterations in pain processing among patients with depression or FMS were reported previously, but this study found that hyperalgesia was more pronounced in patients with FMS than in those with depression [33]. In patients with FMS with comorbid depression or anxiety, pain processing was not altered in comparison to patients with FMS alone [34]. Thus there seems to be an association of chronic pain or depression with altered pain processing, although chronic pain and comorbid depression did not interact with pain processing. 

In regard to anxiety disorders and the neglected role of trauma, a study by Defrin et al. described a unique sensory profile of hyposensitivity to non-noxious stimuli, accompanied by hypoalgesia to at-pain-threshold noxious stimuli and hyper-reactivity to suprathreshold noxious stimuli in patients with PTSD and chronic pain compared with healthy controls [35].

This pattern clearly differs from other patient groups with chronic pain, such as those with fibromyalgia, who tend to exhibit pain hypersensitivity [21,36], and from alterations in PTSD, in which context a decreased sensitivity to painful stimuli has been reported [37,38]. The results reported by Defrin et al. appear to be a hybrid of what has been found in pain-free PTSD patients and PTSD-free pain patients: decreased sensitivity to non-painful stimuli and increased hyperreactivity to painful stimuli. Sensory processing in anxiety disorders other than PTSD is believed not to differ from processing in healthy controls [35]. Another aspect of the psychobiology of pain is pain inhibition. It was found that pain inhibition is deficient in FMS patients but normal in those with depressive disorder [33]. Another study reports evidence that pain inhibition in FMS is more pronounced in patients with comorbid depressive symptoms compared to those with FMS alone [39]. However, due to heterogenic sample selection and different testing methods, the results in regard to pain processing and pain inhibition in chronic pain and mental disorders are inconsistent and partially contradictory [40]. Therefore, a comprehensive measurement of the clinical manifestation and psychobiological aspects of chronic pain is necessary.

To challenge the topic of a mechanism-based subgroup classification of chronic pain patients and to establish specific mechanism-based treatments [41], further variables of interest must be considered to guarantee a more holistic approach, compared to that pursued in prior research. Therefore, we developed a theoretical framework (Figure 1), which investigates the role of chemical sensitisation (nerve growth factor; NGF) [42-46], the endocannabinoid system [47,48], and other psychological variables (e.g. early stress exposure, stress and pain coping, resilience) [49-51] as well as genetic variables [52-54] in addition to mental comorbidity and psychophysiological patterns. NGF is an important key mediator of some forms of persistent pain and plays an important role in the switch from acute to chronic pain as well as the spatial spread of pain [42-46]. The endocannabinoid system refers to a group of neuromodulatory lipids that is relevant for pain memory and pain extinction [47,48]. Accordingly, these variables have proven to be of interest in chronic pain and to be promising in its treatment. In line with that, the current study addresses the association between the clinical manifestation of chronic musculoskeletal pain (including mental comorbidity) and neurobiological changes.

Therefore, the purpose of the present study is to 1) identify and describe subgroups of patients with musculoskeletal pain with regard to clinical manifestation (including mental comorbidity), 2) investigate whether distinct sensory profiles due to different underlying mechanisms can be distinguished in different subgroups of pain patients 3) and to measure plasma nerve growth factor levels and to analyse distinct endocannabinoid profiles in different subgroups of pain patients.

**Figure 1 F1:**
[figure not shown]
Theoretical framework of our project.

## Methods

This study is part of the consortium ‘Localized and Generalized Musculoskeletal Pain: Psychobiological Mechanisms and Implications for Treatment (LOGIN)’ funded by the German Federal Ministry of Research and Education (01EC1010A-F). More details concerning LOGIN can be found elsewhere [55,56]. This report focuses on subproject number six (SP6) ‘Subgroups Characterised by Psychological Trauma, Mental Co-morbidity, and Psychobiological Patterns and Their Specialised Treatment’. All participants must provide written informed consent before inclusion in the study. The study has been approved by the Ethics Research Committee of the Faculty of Medicine, University of Heidelberg (S-261/2010) and will be carried out in compliance with the Helsinki Declaration.

### Design

The study uses a descriptive and exploratory design. We will include 200 patients with chronic musculoskeletal pain from different settings (a population-based setting and a tertiary care setting) and 90 controls (pain-free patients with PTSD, depression, and healthy controls without mental disorders). All participants will undergo a physical examination. The relevant sociodemographics and measures of clinical manifestations of chronic pain are reported in Table 1: measurements of potential pathophysiological mechanisms are reported in Table 2.

**Table 1 T1:** Variables and methods used to assess clinical manifestations of chronic non-specific musculoskeletal pain

**Questionnaires**	**Variables**
Chronic Pain Grade Questionnaire (CPG)* [65,66]	Severity of chronic pain problems (disability, pain intensity)
Pain Experience Scale (SES) [64]	Sensory and affective descriptors of pain
12-Item Short-Form Health Survey (SF-12)* [74,75]	Health-related quality of life
Resilience Scale (RS11)* [97,98]	Resilience (personal competence, acceptance of self and life)
Hospital Anxiety and Depression Scale (HADS-D)* [99,100]	Anxiety and depression
Childhood Trauma Questionnaire (CTQ)* [72,73,101]	Childhood and adolescence maltreatment (physical and emotional abuse, sexual abuse, physical and emotional neglect)
Pain drawing (pain location) [62][63][6]	Perceived location(s) of pain will be assessed using digitised pain drawings. Classification into categories of chronic local and chronic widespread pain.
Sociodemographics (self-report questions)	Age, sex, marital status, education, employment status
**Interviews**	
Structured Clinical Interview for DSM-IV Axis I Disorders + Axis II (SCID I + II)* [69]	DSM-IV Axis-I and Axis-II mental disorders
**Physical examination**	
ACR Criteria for Fibromyalgia (ACR Classification) [62][102]	Tenderpoint count and documentation of specific symptoms
Physical Impairment Scale (PIS) [67]	Physical impairment (total flexion, total extension, average lateral flexion, straight leg raising, spinal tenderness, bilateral active straight leg raising, and sit-up)
Back Performance Scale (BPS) [68]	Disability. Tests of daily activities (Sock Test, Pick-up Test, Roll-up Test, Fingertip-to-Floor Test, and Lift Test)

* German Version.

**Table 2 T2:** Methods used to assess the potential mechanisms involved in chronic non-specific musculoskeletal pain

**Measures**	** *Variables* **
Quantitative Sensory Testing (QST) [76,103]	Comprehensive profiles of somatosensory functions (thermal and mechanical detection and pain thresholds, vibration thresholds, and pain sensitivity to sharp and blunt mechanical stimuli). Discrimination between local vs. generalised and peripheral vs. central nervous mechanisms.
Conditioned Pain Modulation (CPM, the diffuse noxious inhibitory control-like effect) [77,78]	A descending pain inhibitory mechanism that inhibits nociceptive activity arising from the afferent primary fibres at multiple levels of the dorsal horn, resulting in diffuse pain inhibition. These descending pain pathways originate from the brainstem and have significant inhibitory actions on nociceptive activity, thereby affecting pain perception.
*Blood Tests*	
Nerve Growth Factor (NGF)	Plasma NGF levels (proximity ligand ELISA techniques)
Endocannabinoids + related lipids (ECs)	EC (anandamide (AEA), 2-arachidonoyl glycerol (2-AG), 1-arachidonoly glycerol (1-AG), palmitoyl ethanol amine (PEA), oleoyl ethanol amine (OEA), arachidonic acid) in human plasma (large- scale lipidomic profiling using the LC-MS/MS QTrap ABI5500)
Genetics	2* 9 ml EDTA tubes, stored for the second funding period

### Samples and patient recruitment

We will recruit patients with *non-specific chronic musculoskeletal pain* as well as control subjects that are not in pain: 1) Population-based sample: In a previous *population-based* study (“Generalization of Pain: A prospective population-based survey with clinical examination” as part of the German Back Pain Research Network, supported by the Federal Ministry of Education and Research; [21,23,57,58]), we established a representative sample of patients with chronic local and chronic widespread back-pain. For the present study, 100 patients from this representative study sample will be randomly recruited. 2) Tertiary care setting: We will recruit 100 consecutive musculoskeletal pain patients from the *tertiary care Musculoskeletal Pain Centre* at the University Hospital Heidelberg. 3) Control subjects: To determine whether the results are specific for pain, we will further investigate three groups of *pain-free patients*: a) *PTSD* patients (n = 30), b) patients with *depression* (n = 30), and c) *healthy controls* (n = 30). Patients with PTSD and depression will be recruited in our Psychosomatic Outpatient Centre at the University Hospital of Heidelberg. Healthy controls will be recruited by flyers posted around the local community. All groups will be matched with respect to age, sex, and (if appropriate) pain location to our population-based sample. Thus, we will include at least 200 patients with non-specific chronic pain and 90 pain-free subjects.

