#### Pain dimensions

There are at least four dimensions of pain experience that can be distinguished. These are intensity, location, quality, and affect. *Pain intensity*: Pain intensity is defined as how much a person hurts. It will be measured using a numerical rating scale, ranging from 0 ‘no pain’ to 10 ‘worst pain imaginable’. *Pain location*: Pain location can be defined as the perceived location(s) of pain sensations that patients have on or in their body. Spatial distribution patterns (local vs. referred pain) will be assessed using a digitised pain drawings [63]. Moreover, categorisation as CLP, CWP, and FMS will be based on the ACR criteria [62] and a more precise definition elaborated by Harkness et al. [6]. Therefore, each participant will be asked to complete a body pain diagram, marking all areas where pain is experienced. Afterwards, the pain diagram will be discussed jointly by the participant and the physician to rule out any misunderstandings. *Pain quality and pain affect*: Pain quality refers to the specific physical sensations associated with pain. Pain affect is the degree of emotional arousal caused by the sensory experience of pain. The affective and sensory dimensions of pain will be measured using the Pain Experience Scale (SES). The SES is the standard instrument of the German chapter of the International Association for the Study of Pain. The SES consists of 10 items on a sensory subscale (e.g., ‘throbbing’, ‘wrenching’ or ‘stinging’) and 14 items on an affective subscale (e.g., ‘exhausting’, ‘fearful’, or ‘unbearable’). The response format is a four-stage format (0 ‘not appropriate’; 1 ‘somewhat appropriate’; 2 ‘generally appropriate’; 3 ‘fully appropriate’). The sensory score of the SES is the mean of all sensory items; the affective score of the SES is the mean of all affective items. The retest-reliability of the SES lies between .89 and .96, and Cronbach’s Alpha lies between .72 and .92 [64].

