### Statistical analyses

Descriptive statistics will be presented with means and standard deviations for continuous variables and absolute numbers and percentages for categorical variables. Questionnaires will be dealt with according to questionnaire manuals. The prevalence of chronic local pain, chronic widespread pain, fibromyalgia, and mental comorbidities will be determined for the population-based sample and tertiary care setting. Explorative cluster analysis will be conducted to establish subgroups based on the clinical manifestations observed. Therefore, the dimensions of pain (see above) and mental comorbidity will be used as cluster variables. Then, we will explore whether different neurobiological profiles (QST profiles, CPM, NGF levels, EC profiles) correspond with these subgroups. Pain drawings will be scanned, superimposed, and transformed into two-dimensional color-coded images. Body areas with high occurrence of pain will be illustrated in dark red; body areas without pain will appear in white. To classify patients who suffer chronic local pain (CLP) or chronic widespread pain (CWP), pain drawings will be analysed according to the ACR criteria [62] and a more precise definition [6]. Quantitative sensory testing (QST) data pre-processing and statistical analysis will be performed according to the protocol established by Rolke et al. [76]. To quantify conditioned pain modulation (CPM), the PPT before PHP will be subtracted from the PPT after PHP. Negative values indicate an analgesic effect due to CPM. Differences between patient groups will be analysed using analyses of co-variance (ANCOVA), followed by Fisher’s least significant difference test. Potential confounders will be included as covariates, if indicated. QST modalities or CPM will be entered as dependent variables, the patient groups as an independent variable. For more detailed information analysing QST data, we will refer to the protocol proposed by Rolke et al. [76]. The same procedure will be applied with regard to nerve growth factor (NGF) and endocannabinoids (ECs).

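### The tertiary-care sample is described as both consecutive and matched, yet its pain-type and comorbidity proportions are to be reported as tertiary-care prevalence

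*Protocol article*

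**What the plan says.** Three statements in the protocol article bear on the same 100 patients.

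- **Recruitment** (Samples and patient recruitment): "We will recruit 100 consecutive musculoskeletal pain patients" from the tertiary musculoskeletal pain centre.
- **Matching** (same paragraph): "All groups will be matched with respect to age, sex, and (if appropriate) pain location to our population-based sample". The abstract repeats this without the qualifier: "The samples will be pain localisation matched by sex and age to the population-based sample".
- **Reporting** (Statistical analyses): "The prevalence of chronic local pain, chronic widespread pain, fibromyalgia, and mental comorbidities will be determined for the population-based sample and tertiary care setting".

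The matching reference is itself a random draw: "For the present study, 100 patients from this representative study sample will be randomly recruited". Pain location is assessed by pain drawing. Table 1 lists under it "Classification into categories of chronic local and chronic widespread pain", and the section Pain dimensions adds, under the location heading, that "categorisation as CLP, CWP, and FMS will be based on the ACR criteria" and a refined published definition. The article does not say at what level location is matched. It also does not say that tertiary prevalence will be taken from patients before matching or weighted back to the clinic's own mix.

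**The concern.** A consecutive series enrols each eligible attender in turn, and for that reason its proportions can be read as the clinic's case mix. A matched series passes over attenders who do not fit the reference distribution, so its proportions partly reflect the reference. The qualifier in the matching sentence does not exempt the tertiary patients. The three control groups are to be pain-free and the population sample is the reference, so the tertiary sample is the only group for which matching on pain location has any meaning.

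The difficulty is sharper because a matching variable is closely tied to a reported result: CLP and CWP are classified from the pain drawing that records location. What is at stake is the tertiary-care prevalence of CLP, CWP, FMS and mental comorbidity. A reader would take these as a description of the clinic, and a confidence interval would not reveal the selection.

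**Working it through.** **Inputs.** Tertiary n = 100, population n = 100 and three control groups of 30 (Samples and patient recruitment). CLP 61.8% and CWP 38.2% in the earlier population-based study (Sample size estimation). The tertiary CWP share is not given; write it as t and, as an assumption, let it run from 50% to 70%.

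**The plan's own figures.** 100 + 100 = 200 pain patients, 3 × 30 = 90 controls, and 61.8% + 38.2% = 100%. All reproduce.

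**What a matched sample estimates.** Let w be the stratum shares in the population sample, v the stratum shares among eligible tertiary attenders, and p the tertiary prevalence within each stratum.

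- Consecutive sample: expected proportion = Σ v·p
- Matched sample: expected proportion = Σ w·p

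The two agree only if w = v or if p does not vary across strata. This holds for any matching variable, so age and sex matching alone can shift a prevalence that varies with age or sex.

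**CWP, if location is matched at the CLP/CWP level.** Within strata, p is 0 for CLP and 1 for CWP, so the matched share equals w: about 38 CWP and 62 CLP patients, or whatever split the drawn population sample has. The standard error of that split is √(0.382 × 0.618/100) = 0.049, giving a 95% half-width of 1.96 × 0.049 = 0.095. The number of eligible attenders needed to fill 62 CLP places is about 62/(1 − t).

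| Assumed t | Matched share minus t | Eligible attenders needed | Passed over |
|---|---|---|---|
| 50% | 38 − 50 = −12 points | 62/0.50 = 124 | 24 |
| 60% | 38 − 60 = −22 points | 62/0.40 = 155 | 55 |
| 70% | 38 − 70 = −32 points | 62/0.30 ≈ 207 | 107 |

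If t were itself 38.2%, the bias would be essentially nil.

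**FMS.** If FMS is counted within CWP, it cannot exceed about 38% of the matched sample. If a share f of CWP patients have FMS, the matched sample gives 0.38f where the clinic has t·f. Table 1 also requires a tender point count, so FMS is capped and shifted but not fixed.

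**Mental comorbidity.** With prevalence a in CLP and b in CWP, the matched value is 0.618a + 0.382b and the clinic value is (1 − t)a + t·b. The difference is (0.382 − t)(b − a). For t from 50% to 70%, this is about 12% to 32% of the gap between b and a, and zero if there is no gap. The article gives neither a nor b.

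**If the tertiary sample were kept consecutive.** The 95% half-width for the CWP share at n = 100 would be 9.8, 9.6 and 9.0 points at t = 50%, 60% and 70%.

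The population-based prevalences are not affected, because that sample is the reference.

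**The case against.** The strongest reply is that the level of location matching is not stated. The section Pain dimensions first defines location as where pain is felt, and the CLP/CWP/FMS categories come as a further step. The population sample consists of back-pain patients while the clinic recruits musculoskeletal pain patients more broadly, so matching on body region is a plausible reading. It would constrain the CLP/CWP split less. This stands: a reader might infer that the tertiary CWP share is fixed at 38.2% whatever the truth, and the article does not support that.

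It can also be said that attenders may be screened consecutively and enrolled if they meet a matching rule. That is a workable procedure, and its details commonly sit in a full protocol. It does not remove the problem, because the enrolled patients are still selected and the article reports their proportions as the setting's prevalence.

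A reader might further infer that the study will claim equal pain extent in the two settings. No test of prevalence between settings is stated; the plan is to describe each sample. The 50% to 70% range has no basis in the article, which anticipates more depression and anxiety in tertiary care but says nothing of the CWP share there.

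Finally, matching the two pain samples is defensible if the aim is to compare mechanism measures across settings. That is accepted. The objection is only to reading prevalence off the matched sample.

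**Conclusion.** The point holds as a should-fix. As written, the same 100 patients are consecutive, matched, and the source of tertiary-care prevalence. Unless the clinic's mix already resembles that of the population sample, or the prevalences do not depend on the matching variables, the reported tertiary figures will be distorted by selection.

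The size cannot be determined from the article. The 12 to 32 points for CWP rest on two assumptions: matching at the CLP/CWP level and a true tertiary share of 50% to 70%. With coarser location matching the effect would be smaller. FMS is capped or shifted, and comorbidity moves only as far as it varies with the matching variables.

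The severity is limited because prevalence is a descriptive output and not one of the three objectives, which concern clinical subgroups, sensory profiles and plasma markers. The descriptive design does not excuse the conflict, since these proportions are among the results to be presented.

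**What to change.** State which rule governs the tertiary sample and, if matching stays, at what level location is matched. Then take one of two routes.

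1. **Keep the sample consecutive.** Drop location matching for it, and say how age and sex matching is to be reconciled with consecutive enrolment, since that alone can shift prevalence. Adjust population-versus-tertiary comparisons for age, sex and CLP/CWP status. Do not carry the CLP/CWP covariate into comparisons between clusters: the clusters are built partly on pain location, and the adjustment would remove part of the contrast under study. Cost: some loss of balance between the two pain samples.
2. **Keep the matching.** Take tertiary prevalence from a log of all consecutive eligible attenders before matching, recording age, sex, CLP/CWP/FMS class and, if its prevalence is to be reported, mental comorbidity. If a log is not feasible, or comorbidity cannot be assessed in those passed over, present the affected proportions as a description of the matched sample and not as tertiary-care prevalence. Cost: a simple screening log, or the loss of a few descriptive figures.

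The choice should be made before recruitment starts, because attenders passed over without a record cannot be recovered later.
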